#### Randomisation

GP practices will be randomised to intervention or to treatment as usual on a 1:1 basis by a statistician not otherwise involved in the programme based at the University College London PRIMENT Clinical Trials Unit. The trial manager will communicate the results of randomisation to the practices.

There should be the same number of GP practices recruited to the intervention and usual care. This will be achieved using block randomisation. The size of the blocks is at the discretion of the independent statistician, who will not divulge this to the trial management group, senior statistician, trial statistician or health economists until the allocation code is broken and the information is needed to write up the trial. Figure 1 demonstrates the recruitment pathway through the study.

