### Statistics and data analysis

#### Sample size

A total of 350 people from 70 GP practices will be recruited in to the study. In determining the size of the trial, we considered 1) important effect sizes, 2) size of clusters, and 3) attrition.

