#### Effect size

Our primary outcome is total cholesterol. Two community studies of UK adults with SMI reveal mean total cholesterol levels of 5.4 mmol/l (standard deviation (SD) 1.3) [14] and 5.7 mmol/l (SD 1.4) [51].

We consider an effect size of 0.4 SDs difference in cholesterol, between the two trial arms, to be the minimum clinically important difference. Statins usually have far greater effect sizes, approaching two SDs [52], however in this effectiveness trial, we are comparing a behavioural intervention with treatment as usual, so cannot expect effects as large as this. Based on a two-sample t-test, to detect a difference of 0.4 x (1.3 mmol/l) requires 132 participants per arm, with 90 % power and 5 % significance level.

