#### Sample size inflation for clustering and attrition

To account for the cluster effect, we have assumed that five participants on average will be recruited per practice. Dropout rates in the SMI trials are <20 % at 12 months [30, 53]. Using an intra-class correlation coefficient of 0.02 for trials in primary care [54] and an average cluster size of four participants per practice (after allowing for 20 % attrition) yields 140 participants per arm. Inflating this figure for 20 % attrition and rounding up results equates to a total of 350 participants and 70 GP practices for the trial.

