#### Statistical analysis

All analyses will be on an intention-to-treat basis. Statistical analyses will be carried out using Stata [55]. We will produce summary statistics for all variables, both overall and by randomised group. Summary statistics for continuous variables will be mean or median, (with SD, or interquartile range) as appropriate, and for categorical variables, frequency and percentage within each category.

The primary outcome will be analysed using a linear random effects regression model adjusting for the baseline cholesterol, whilst accounting for clustering as a random effect (GP practice). Results will be presented as mean difference between randomised arms with 95 % confidence interval and *P* value.

Appropriate analogous random effects regression models will be used to analyse the secondary outcomes.

For both the primary and continuous secondary outcomes, the residuals will be checked for normality. If they are not normally distributed, outcomes may be transformed. If it is necessary to categorise outcomes, it will be done with clinical input.

Complete case analyses will be the main analyses from this study. Bias due to missing data will be investigated. A supportive analysis will include adjusting for predictors of missingness that are related to outcome, if necessary, and adjusting for factors that have baseline imbalances that are related to the outcome. If the proportion of non-adherence is greater than 5 %, an appropriate analysis accounting for non-adherence will be considered. Those in the treatment-as-usual practices will be assigned an adherence score equivalent to no adherence to the intervention. If it is appropriate to carry out this analysis, it will be done once the statistician has been unblinded to randomised group. Results from the analysis of secondary outcomes and supportive analyses will be presented as estimates with 95 % confidence intervals.

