#### Economic evaluation

The aim of the economic evaluation is to report the mean incremental cost of the PRIMROSE intervention compared to treatment as usual in the reduction of CVD risk in people with SMI, from the NHS perspective in the primary analysis and from a societal perspective in a secondary analysis. The primary effectiveness outcome, as recommended by NICE, will be quality-adjusted life years (QALYs) [56]. Responses to the EQ-5D-5 L questionnaire collected during the trial will be used in conjunction with EQ-5D-5 L specific valuation sets [47] to calculate utility scores over a time horizon of 1 year. Baseline differences in utility scores will be adjusted for using regression analysis. The cost of the intervention will include the cost of the printed materials, training, clinical tests and other consumables used during the intervention and nurse/HCA time spent delivering the intervention. The cost-components that will be included in the health care perspective analysis for arms of the trial include new prescriptions during the study follow-up period, general and psychiatric hospital admissions, A&E contacts; outpatient visits, primary care contacts and community service use. Informal care arrangements, changes in living situation, carer costs, and out-of-pocket costs for services such as weight-management programmes, gym and leisure activities, smoking cessation and community service use [48] will be included in the societal perspective analysis. Unit costs will be obtained from the Personal Social Services Research Unit (PSSRU) [57], reference costs [58], British National Formulary (BNF) [59] and other national sources of costing information. Cost-effectiveness will be reported as the mean incremental cost per QALY gained of the PRIMROSE intervention versus treatment as usual. All cost-effectiveness analyses will conform to the recommended methodology [56]. Bootstrapping will be used to derive 95 % confidence intervals for mean cost and QALYs for the two trial groups, 95 % confidence intervals around the incremental cost-effectiveness ratios and cost-effectiveness acceptability curves and cost-effectiveness planes. The analyses will be subjected to one-way and two-way sensitivity analyses to test any assumptions made in the analysis. Trial results will also be used to update a long-run CVD cost-effectiveness model, extrapolating costs and consequences to a 10-year time horizon using discrete event-simulation.

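### The planned 95% confidence interval around the ICER has no fallback and may be uninterpretable if the one-year QALY difference is near zero; incremental net monetary benefit, bootstrapped by practice, would avoid this

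*Protocol article*

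**What the plan says.** The Economic evaluation section measures effect in QALYs from EQ-5D-5L responses over one year and reports the incremental cost per additional QALY. Baseline utility is adjusted for by regression. On uncertainty it says "Bootstrapping will be used to derive 95 % confidence intervals for mean cost and QALYs for the two trial groups", followed by "95 % confidence intervals around the incremental cost-effectiveness ratios and cost-effectiveness acceptability curves" and cost-effectiveness planes. It does not describe what will be reported if the ratio interval cannot be interpreted. It names neither the unit to be resampled nor the form of the regression.

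Elsewhere the design is explicit about clustering. Under Randomisation, "GP practices will be randomised to intervention or to treatment as usual on a 1:1 basis". Under Statistical analysis, the primary model adjusts for baseline cholesterol "whilst accounting for clustering as a random effect (GP practice", and the secondary outcomes get corresponding random-effects models. The sample size section also inflates for clustering: "Using an intra-class correlation coefficient of 0.02 for trials in primary care".

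**The concern.** The ICER is a ratio, the cost difference divided by the QALY difference. When the denominator can be zero or negative, the ratio no longer orders outcomes from good to bad. A negative value can mean cheaper and better, or dearer and worse. A positive value can mean a gain bought at a cost, or a loss accepted for a saving. Very large positive and very large negative values sit next to each other, either side of a zero QALY difference. Sorting such replicates to find two limits mixes conclusions that are opposite in meaning.

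Three features of the trial make a small one-year QALY difference plausible. People with existing CVD are excluded. The primary outcome is a risk marker, total cholesterol. The within-trial horizon is one year, and longer-run consequences are left to a ten-year simulation model. Cost-effectiveness is part of the trial's stated aim, and the only interval planned for the cost-per-QALY comparison itself is the one that may fail.

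A second, smaller matter belongs in the same edit. Every economic interval and curve comes from the bootstrap, so the resampling unit should match the unit of randomisation.

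**Working it through.** **The plan's own figures.** Inputs from the Sample size sections: "to detect a difference of 0.4 x (1.3 mmol/l) requires 132 participants per arm", "with 90 % power and 5 % significance level"; ICC 0.02; four analysed per practice after 20% attrition; "A total of 350 people from 70 GP practices will be recruited in to the study".

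- A two-sided calculation at 0.4 SD gives 132 per arm, as stated.
- Design effect: 1 + (4 − 1) × 0.02 = 1.06.
- 132 × 1.06 = 139.9, i.e. 140 per arm analysed.
- 140 / 0.8 = 175 per arm, or 350 in total.

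All of these reproduce. The economic section states no sample size or precision figure of its own.

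**How often replicates cross zero on the QALY axis.** The article gives no QALY SD, so 0.15, 0.20 and 0.25 are assumptions. With 140 analysed per arm and design effect 1.06:

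SE = SD × √(2 × 1.06 / 140) = SD × 0.123

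Share of replicates below zero = Φ(−difference / SE), with the replicates centred on the difference shown.

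| QALY difference | SD 0.15 (SE 0.0185) | SD 0.20 (SE 0.0246) | SD 0.25 (SE 0.0308) |
|---|---|---|---|
| 0 | 50% | 50% | 50% |
| 0.01 | 29% | 34% | 37% |
| 0.02 | 14% | 21% | 26% |
| 0.05 | 0.3% | 2% | 5% |
| 0.10 | about 0 | about 0 | 0.1% |

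More than 2.5% of replicates lie below zero whenever a positive difference is smaller than 1.96 × SE. That is 0.036, 0.048 and 0.060 for the three SDs. Below those values a 95% interval for the ratio cannot be formed from one side of the axis alone.

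**The alternative.** Incremental net monetary benefit at threshold λ is λ × (QALY difference) − (cost difference). It is linear in both quantities and has no denominator. Its interval therefore exists and keeps its ordering whatever the QALY difference, and it comes from the same replicates.

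**Clustering, if participants were resampled as independent.** With m = 4 analysed per practice, the design effect is 1 + 3 × ICC. The interval is too narrow by 1 − 1/√(design effect). A nominal 95% interval covers 2Φ(1.96/√(design effect)) − 1.

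| ICC | Design effect | Too narrow by | Coverage |
|---|---|---|---|
| 0.02 (article) | 1.06 | 2.9% | 94.3% |
| 0.05 (assumed) | 1.15 | 6.7% | 93.2% |
| 0.10 (assumed) | 1.30 | 12.3% | 91.4% |

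The article gives no ICC for costs or QALYs.

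**The case against.** **On the ratio interval.** Whether replicates cross zero depends on data not yet collected, and the article does not specify a percentile interval. The same sentence commits to planes and acceptability curves. These survive a near-zero QALY difference, and the curves already express net benefit across thresholds. All of this is correct, and it means that a decision need not rest on the ICER interval. A reader might infer that the interval is bound to be meaningless in this trial. The article does not support that: at a difference of 0.10 essentially no replicates are negative. What stands is that an explicit commitment has been made to a summary that fails in a plausible scenario, with nothing named in its place.

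**On clustering.** A reader might infer that the economic analysis ignores practices, so that its intervals will be too narrow. The section does not say so. A bootstrap can resample practices and a regression can carry a practice effect. A condensed article commonly leaves this detail to a fuller plan, and the section refers to a recommended methodology. Quality of life, measured by EQ-5D-5L, also falls under the random-effects models for secondary outcomes. The silence is therefore no error in itself.

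It is also tempting to argue that costs cluster more than cholesterol, because training and nurse time belong to the practice. But the cost list also includes admissions, emergency contacts and outpatient visits, which depend on the individual. No figure in the article settles the matter.

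**On importance.** Cost-effectiveness might be read as ranking equally with the clinical question. It is in the overall aim, but the single primary objective is total cholesterol, and the trial is sized on that alone.

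**Conclusion.** The point holds in conditional form. The plan commits to a confidence interval around the ICER without a fallback, and that interval will not be interpretable if the one-year QALY difference is near zero. On an assumed QALY SD of 0.20, about a third of replicates would be negative at a difference of 0.01 and about a fifth at 0.02. Across SDs of 0.15 to 0.25 the share at 0.02 is 14% to 26%. These figures rest on the assumed SDs, on 140 analysed per arm and on a design effect of 1.06. The planes and acceptability curves keep the damage modest.

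The clustering element is an alignment to make in the same edit and not a demonstrated fault. At the article's own ICC, even resampling participants as independent would cost about 3% of interval width. A material loss needs a larger ICC, which would be an assumption.

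**What to change.** In the Economic evaluation section:

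1. Replace the confidence interval around the ICER with incremental net monetary benefit and its 95% confidence interval, at willingness-to-pay thresholds named in advance. Keep the ICER point estimate, the plane and the acceptability curve.
2. State that the bootstrap resamples practices within arm, or is two-stage (practices, then participants, with a shrinkage correction). Keep each participant's cost and QALY together so that their correlation is preserved.
3. State that the cost and QALY regressions include a GP-practice effect, in line with the Statistical analysis section.

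This needs no new data and no change to design or sample size. The cost is a few lines of text and modest programming. If participants would otherwise have been resampled as independent, intervals widen by a factor of about 1.03 at ICC 0.02 (√1.06) and 1.14 at an assumed 0.10 (√1.30).

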### Research governance

We will work with the Clinical Research Networks (CRNs) to identify expressions of interest from GP practices to take part in the study.

A trial management subgroup will meet monthly at the start of the trial to monitor progress. At trial month 3, the group will review the effectiveness of research procedures in the first wave of practices and amend the protocol if necessary. Meetings will decrease to 3-monthly from month 18 of the trial onwards. There will also be an externally chaired trial steering committee meeting twice per year.

The trial will be fully registered and managed through the PRIMENT clinical trials unit (http://www.ucl.ac.uk/pcph/priment), which specialises in trials in mental health and primary care. PRIMENT will oversee the design, randomisation of practices, web-based data entry, all trial monitoring and the analysis plan. Data management will also be overseen by the PRIMENT clinical trials unit, with data being held for a minimum of 20 years from completion of the study according to University College London requirements.

### Adverse events

All GP practices and research nurses will be trained in reporting adverse events procedure. If an event occurs, they will be instructed to telephone the trial manager within 24 hours of becoming aware of the event. They will then be asked to complete an adverse event form and submit this to the trial manager. Adverse events will be assessed by the chief investigator, considered at trial management team meetings and reported to the study sponsor.

### Ethics approval

Ethics approval was obtained from the City Road and Hampstead Research Ethics Committee (Reference No: 12/LO/1934, approval granted 10 January 2013). Local NHS approvals are being obtained before the start of each recruitment wave from the following research and development (R&D) departments: North and Central London research consortium (Noclor), Wessex primary care research support service, Northamptonshire research and development service, North of England commissioning support unit, Avon primary care collaborative, Lincolnshire community health services NHS trust, clinical research network: North West Coast clinical commissioning group, Norfolk & Suffolk primary & community care research office, Leicester City clinical commissioning group, South London clinical research network, West Midlands Primary Care RM&G business support service and clinical research network: West Midlands, research support team. The trial has been allocated an International Standard Randomised Controlled Trials Number (ISRCTN13762819).

### Study sponsorship

Camden and Islington NHS Foundation Trust is the trial sponsor.

## Discussion

The PRIMROSE intervention has been developed using evidence from the literature, focus groups and workshops with key stakeholders. The intervention is underpinned by a theoretical framework [36], which was applied to the development work findings in order to select simple behaviour change strategies that can be used by practice nurses or HCAs, with minimal training, and incorporated into time-limited primary care consultations.

Existing reviews identify a need for interventions that tackle multiple cardiovascular risk factors in people with SMI [60]. Many of the interventions that have been tested in this group have been intensive behavioural interventions for weight loss or smoking cessation, delivered in secondary care settings by research therapists [61, 62]. The PRIMROSE study is a pragmatic trial with the intervention being delivered by a practice nurse/HCA at each participant’s GP practice. It may be possible to implement this model as part of routine clinical primary care, for example, in a UK setting as part of an Enhanced Service Model [63].

Offering cardiovascular risk lowering interventions to people with severe mental illnesses may provide an opportunity for early intervention and prevention before cardiovascular events occur. Physical health checks for people with SMI can be limited and are often opportunistic [33]. The PRIMROSE intervention seeks to address this issue, offering intensive consultations over a 6-month period that complement the clinical skills of practice nurses or HCAs to manage multiple CVD risk factors.

The results will assess the impact of the intervention on total cholesterol at 12-month follow-up. The impact of the intervention on secondary outcomes of health behaviours, quality of life, well-being, medication adherence, service use and medication prescriptions will be measured. The cost effectiveness of the intervention will also be determined.

### Dissemination

We will disseminate the results of the study through social media, the Lived Experience Advisory Group and through summary reports of findings to all key stakeholders involved in the study.

### Trial status

The trial is currently ongoing.

## Abbreviations

A&E: Accident and Emergency
AUDIT-C: Alcohol Use Disorders Identification Test Consumption
BMI: Body Mass Index
BNF: British National Formulary
COM-B model: Capability Opportunity Motivation – Behaviour model
CRN: Clinical Research Network
CSQ: Client Satisfaction Questionnaire
CSRI: Client Service Receipt Inventory
CVD: Cardiovascular Disease
DINE: Dietary Instrument for Nutrition Education
DNA: Deoxyribonucleic Acid
EHHaL: Employment Housing, Health and Leisure Questionnaire
GP: General Practitioner
HbA_1c_: Glycated Haemoglobin
HCA: Healthcare Assistant
HDL: High Density Lipoporotein cholesterol
IPAQ: International Physical Activity Questionnaire
LDL cholesterol: Low Density Lipoprotein cholesterol
LEAP: Lived Experience Advisory Panel
MMS: Morisky Scale of Adherence Questionnaire
NHS: National Health Service
NICE: The National Institute for Health and Care Excellence
NIHR: National Institute for Health Research
PGfAR: Programme Grants for Applied Research
PSSRU: Personal Social Services Research Unit
QALY: Quality-Adjusted Life Year
QoF: Quality Outcomes Framework
SD: Standard Deviation
SMI: Severe Mental Illness
TAU: Treatment as Usual
TDF: Theoretical Domains Framework
WEMWEBS: Warwick Edinburgh Mental Wellbeing Scale
